Although multiple studies have demonstrated many benefits of exercise for men with PC on ADT, the strongest and most consistent benefits have been shown with 1:1 supervised (i.e. personal training), in-centre interventions [100]. As summarized in recent reviews [81, 82, 101], four trials have featured 1:1 supervised exercise interventions, all of which reported positive effects on QOL or fitness outcomes. Two studies (only one was randomized) were group-supervised interventions, and both showed benefits in QOL and/or fitness outcomes. In contrast, of the four home-based studies (two randomized controlled trials (RCTs)), only two were positive, and the magnitude and breadth of benefits were smaller than with supervised exercise interventions. Of note, these three exercise delivery models have not been directly compared to one another. Prior trials have used different outcome measures, assessment time points, and training routines, making indirect comparisons difficult.

Despite the accumulating evidence of benefits, few men with PC, including those on ADT, exercise regularly [99, 102–105]. For exercise interventions to be most useful to men on ADT, long-term exercise adherence and benefits must be achieved. Long-term exercise adherence has been defined as engaging in regular exercise for at least 6 months post-intervention [106]. In the general population, about 50% of individuals stop exercising after 6 months. Experience with cancer survivors suggests that they fare no better [107]. Cessation of exercise leads to loss of benefits in virtually every setting [108]. Unfortunately, most previous research in men on ADT has been limited to reporting exercise benefits and adherence only to the end of the supervised exercise intervention [79, 80]. In two studies examining participants 4–6 months post intervention, weekly exercise was reduced and QOL benefits were diminished over time [69, 74].

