Given the gaps in the published evidence, we recently conducted a phase II trial to assess the feasibility and efficacy of these 3 delivery models in a 6-month intervention [113] (manuscript submitted). The preliminary results suggested that group-supervised exercise and home-based exercise were generally non-inferior to 1:1 supervised exercise for both QOL and fitness outcomes. Specifically, group-supervised exercise was shown to have less than a 20% probability of being inferior to 1:1 exercise for 2 of 3 QOL and 3 of 3 fitness outcomes. The home-based arm had less than a 25% probability of being inferior to the 1:1 arm for 1 of 3 QOL and 3 of 3 fitness outcomes. Moreover, the home-based arm was associated with the highest adherence based on accelerometry. Altogether, this provided a foundation to refine our phase II protocol and conduct the present phase III trial, in which we decided to directly compare 2 exercise delivery methods that are least resource intensive. Although efficacious, the 1:1 supervised intervention arm appeared to provide minimal benefit over a group-supervised program and is cost-prohibitive within a publicly funded health care system.

The primary aims of this phase III non-inferiority RCT are:i.To determine, in men with PC on ADT, whether a home-based supported exercise program is non-inferior to a group supervised in-centre (facility-based) exercise program on the primary outcomes of fatigue and functional endurance;ii.To examine adherence to exercise and predictors of adherence in each exercise group during the 6-month intervention and for 6 months after program completion;iii.To conduct an economic analysis comparing both exercise interventions and usual care.

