### Sample size calculation

A total of 200 participants (100 per arm) gives an estimated 81% power for analysis of the FACT-F and 6MWT for non-inferiority and will also provide accurate estimates of parameters related to secondary outcomes. Details are shown in Additional file 4: Methods. There are no planned interim analyses or early stopping rules.

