### Statistical analysis

#### Co-primary outcomes

The primary analysis will use a Bayesian analysis of covariance (ANCOVA) model to regress the change in FACT-F and 6MWT values between baseline and 6 months against the baseline value, the treatment group variable and variables representing stratification by centre and length-of-ADT. We will treat the high-intensity group (group supervised; higher level of supervision and greater resources) as the reference.

For each primary outcome, we will compute the Bayesian posterior probability that the low intensity group is non-inferior to the high intensity group (i.e., that the mean difference between groups is larger than the non-inferiority margin -**δ**). If either of these probabilities is large enough (i.e. > 97.5%) then we will declare the home-based group to be non-inferior for that outcome. One advantage of a Bayesian approach is that it allows us to assign posterior probabilities to the 4 possible outcomes of the study (illustrated in Fig. 3): (1) Home-based inferior only for 6MWT; (2) Home-based inferior only for FACT-F; (3) Home-based inferior for both outcomes; and (4) both non-inferior. Another advantage is that it allows a more useful presentation of individual results than a simple confidence interval or *p*-value: for example, we will be able to say that the mean difference lies below –**δ** (i.e., home-based is inferior) with probability X%, that it lies between –**δ** and 0 (i.e., home-based is worse but non-inferior) with probability Y% and that it is above 0 (i.e., home-based is better) with probability Z%. Finally, the outputs of the Bayesian model can be used as probabilistic inputs for the economic analysis. The Bayesian analyses will use non-informative priors, allowing the results to be data-driven and make direct probability statements about non-inferiority.

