**Fig. 3 Fig3:**
[figure not shown]
Illustration of Four Possible Scenarios in Non-Inferiority Testing for Proposed 2-Arm Trial. We will compare groups by means of ANCOVA using the baseline score as the covariate. After fitting a Bayesian model to each outcome, we will evaluate the probability in each of the 4 regions in the figure above. We can calculate the probability that: 1. Both the 6MWT and FACT-F fatigue scores are non-inferior in the home-based arm. This is the green region (**b**). 2. Both the 6MWT and FACT-F fatigue scores are inferior in the home-based arm. This is the grey region (**c**). 3. The 6MWT score is non-inferior in the home-based arm. This is the green region (**b**) plus the blue region (**a**). 4. The FACT-F Fatigue score is non-inferior in the home-based arm. This is the green region (**b**) plus the gold region (**d**). If either probability in (3) or (4) is above 97.5%, then we will declare non-inferiority of the home-based intervention.

Since this is a non-inferiority trial, the primary analysis will be per protocol, which in the presence of non-adherence to exercise is more conservative than intention-to-treat (i.e., less likely to conclude groups are similar when they are not). Two secondary analyses of the primary outcomes will be conducted. First, we will make the above between-group comparison of the changes in FACT-F and 6MWT scores from baseline to each follow-up time point. Secondly, we will perform an intention-to-treat analysis, including outcomes on subjects who were non-adherent to their exercise program. We will also conduct within-group analyses of change over time for the co-primary outcomes to understand the effects of each exercise modality on these outcomes and to facilitate comparisons with published studies.

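### Per protocol is made primary as the conservative choice, but adherence is itself an effect of the delivery model, so excluding non-adherers can bias the comparison in either direction

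*Protocol article*

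**What the plan says.** In the Protocol article, Statistical analysis, Co-primary outcomes (the text after the Fig. 3 legend), the choice of analysis set is justified in one clause: "the primary analysis will be per protocol, which in the presence of non-adherence to exercise is more conservative than intention-to-treat". ITT follows as the second of two secondary analyses: "we will perform an intention-to-treat analysis, including outcomes on subjects who were non-adherent to their exercise program". By contrast with that description, the per-protocol set leaves non-adherent men out.

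The decision rule in the same section is Bayesian with non-informative priors: "If either of these probabilities is large enough (i.e. > 97.5%) then we will declare the home-based group to be non-inferior", applied outcome by outcome.

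Elsewhere the article treats adherence as something the delivery model produces:
- Aim ii, at the end of Background, is to study adherence and its predictors in each exercise group.
- Outcomes and measures, Adherence, defines the primary adherence measure by arm at 3 and 6 months. Statistical analysis, Adherence, tests it between arms.
- Intervention, Home-based program, adds smartphones, Fitbits and coaches in order to raise participation and adherence.
- Background reports that adherence differed by delivery model in earlier work. It was greater with home-based delivery in a review of cardiac rehabilitation trials, and in phase II "the home-based arm was associated with the highest adherence based on accelerometry".

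On power, Sample size calculation says "A total of 200 participants (100 per arm) gives an estimated 81% power for analysis of the FACT-F and 6MWT for non-inferiority" and adds "Details are shown in Additional file 4: Methods". That file is not shown.

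**The concern.** The usual argument for per protocol in a non-inferiority trial is that non-adherence dilutes a real difference, so that including non-adherers makes the arms look alike. That argument fits a trial in which non-adherence is a nuisance that affects both arms in much the same way. Here frequency, intensity, time and type of exercise are meant to be the same in both arms, and what differs is how the exercise is delivered. Adherence is therefore a main route by which one arm could do better or worse than the other.

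Selecting on adherence removes that route from the comparison and sets self-selected men in one arm against differently self-selected men in the other. If unsupervised men adhere less, the cause of home-based inferiority is removed from the data. If they adhere more, a real home-based advantage is removed. In neither case does the primary analysis answer the question in aim i, whether a home-based programme is non-inferior to a group programme. The conclusion of the trial would rest on a non-randomised contrast whose bias has no known sign.

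**Working it through.** **Inputs from the article.** 100 men per arm, 1:1 allocation, 81% power, and a threshold of 97.5% posterior probability. With non-informative priors that threshold acts like a one-sided 0.025 test.

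**Inputs not in the article.** The margin appears only as a symbol. The SD, the assumed true difference, the allowance for loss and the analysis set behind the 81% are in a file that is not shown. The plan's 81% therefore cannot be reproduced independently; it can only be used to back-solve a margin.

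**Step 1: implied margin.** Take a true difference of 0 and 100 analysed per arm:

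margin/SD = (z₀.₉₇₅ + z₀.₈₁) × √(2/100) = (1.960 + 0.878) × 0.1414 = 0.401.

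Other readings of the 81% give 0.458 (both outcomes, independent), 0.300 (either outcome, independent), or 0.423 to 0.449 (81% after 10% to 20% loss).

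**Step 2: model for the bias.** Assume that adherers do equally well in both arms and that adhering is worth e SD over not adhering. Let p_G and p_H be the proportions adhering in the group and home arms.

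- True difference as delivered (home minus group): D = (p_H − p_G) × e.
- ITT: P(declare) = Φ[(0.401 + D)/√(1/100 + 1/100) − 1.96].
- Per protocol: the difference among adherers is 0, so P(declare) = Φ[0.401/√(1/(100p_G) + 1/(100p_H)) − 1.96].

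The adherence and effect values are assumptions; the article gives none for this trial.

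| Adherence group / home | e (SD) | D (SD) | Per protocol | ITT |
|---|---|---|---|---|
| 75% / 35% | 1.0 | −0.40 (at the margin) | 50% | 2.6% |
| 80% / 30% | 1.0 | −0.50 (beyond the margin) | 47% | 0.4% |
| 80% / 50% | 0.6 | −0.18 | 60% | 35% |
| 70% / 30% | 0.5 | −0.20 | 45% | 30% |
| 50% / 80% | 0.6 | +0.18 | 60% | 98% |
| 30% / 70% | 0.5 | +0.20 | 45% | 99% |

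For the top row:
- Per protocol: √(1/75 + 1/35) = 0.2047; 0.401/0.2047 − 1.96 = 0.00, and Φ = 50%.
- ITT: (0.401 − 0.400)/0.1414 − 1.96 = −1.95, and Φ = 2.6%.

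In the first four rows per protocol declares non-inferiority more often than ITT although it has fewer patients. In the last two it declares less often.

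**Step 3: sensitivity to the back-solved margin.** Top row again, at the lowest and highest margins from step 1:
- Margin 0.300: per protocol Φ(0.300/0.2047 − 1.96) = 31%; ITT Φ((0.300 − 0.400)/0.1414 − 1.96) = 0.4%.
- Margin 0.458: per protocol Φ(0.458/0.2047 − 1.96) = 61%; ITT Φ((0.458 − 0.400)/0.1414 − 1.96) = 6%.

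The size of the gap changes but its direction does not.

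**Step 4: power, conditional only.** If the 81% assumes 100 analysed per arm with no allowance for exclusions, power with n per arm is Φ[0.401/√(2/n) − 1.96]: 72% at 80, 66% at 70 and 52% at 50.

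**The case against.** **The evidence in the article points the other way.** Both sources it cites on adherence by delivery model favour home-based delivery, and the home arm here has been strengthened since phase II with Fitbits and monthly in-person coaching. On that evidence per protocol would work against the home arm, which is the caution the plan intends. This stands. A reader might infer that per protocol will hide home-based inferiority; the documents support only that it can. Nor is per protocol conservative only when adherence is similar across arms: the last two rows of the table show it being so with dissimilar adherence. But a rule that is cautious in one direction and lenient in the other, depending on a result not yet known, cannot be justified as conservative in general. In the cautious direction, the caution comes from discarding a real benefit.

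**Loss of power is not shown.** A reader might infer that per protocol undermines the stated 81%. The documents do not support this, because the sample-size inputs are in a file that is not shown and may already allow for exclusions.

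**The adherence levels are guesses.** This also stands. The Background figure that "about 50% of individuals stop exercising after 6 months" concerns the general population and does not give a rate for a supported programme assessed at its end at 6 months. The team's pilot of supervised delivery reported high adherence.

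**ITT is already planned.** True, so a conflict would be visible. But the article's justification gives the per-protocol result priority, and it does not say what follows if the two disagree.

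**Conclusion.** The concern holds in this form: the stated reason for making per protocol primary is not valid as a general claim for a comparison of delivery models, because excluding non-adherers conditions on an effect of the treatment under test. The bias can go either way. At a true deficit equal to the margin, the chance of wrongly declaring non-inferiority could be about 50% per protocol against 2.6% under ITT. Where home-based adherence is higher, the chance of a correct declaration could fall from 99% to 45%. These figures rest on assumed adherence (75%/35% and 30%/70%), assumed effects of adhering (1.0 and 0.5 SD), equal results among adherers in both arms, and a margin of 0.40 SD back-solved from the 81%. They show what is possible and are not a forecast. The conclusion does not depend on the power figures, which remain conditional.

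**What to change.** 1. Delete the statement that per protocol is the more conservative analysis.
2. Raise the planned ITT ANCOVA (all randomised men with outcome data, analysed as allocated) from secondary to co-primary with per protocol.
3. Declare non-inferiority for an outcome only if its posterior probability exceeds 97.5% in both sets.
4. State which analysis set the 81% refers to and, if it is all 200 men, give the power at the per-protocol size expected.

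**Cost.** No new data are needed and the ITT analysis is already planned. The success criterion becomes harder, and joint power can be no higher than that of the per-protocol set: at most about 72%, 66% or 52% with 80, 70 or 50 per arm, on the condition in step 4 of the working. Requiring both sets guards against a false declaration of non-inferiority. It does not recover a home-based advantage lost in the per-protocol set: in the 30%/70% example success stays at or below 45%.

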#### Secondary outcomes

Analyses for each of our secondary outcomes (QOL, fitness, biological, and body composition) will use mixed effects models for data at all time points incorporating within-person correlation. Within-person correlation of residuals will be handled by an autoregressive (AR1) error structure and factors will also be added for the 2 stratification variables (centre, ADT duration). All of these secondary outcomes will be analyzed as continuous variables after examining distributions to ensure symmetrical (approximately normal) distributions. Skewed data will be transformed as appropriate.

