#### Post-intervention period outcomes

Using similar mixed effects models, we will estimate changes over time and differences between exercise delivery groups in FACT-F and 6MWT during the 6-month post-intervention period, covering 3 assessment points (end of intervention, 3 months post-intervention, and 6 months post-intervention).

To give a quantitative overview of changes between and within groups over the entire 12 months, all study outcomes will be assessed using these same types of linear mixed effects models. By examination of estimated model parameters and their 95% confidence intervals, we can assess whether changes over time are similar between groups and whether differences between groups at any given time are clinically important.

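### The mixed models for secondary and post-intervention outcomes name no baseline adjustment, so as written their arm contrasts are less precise than the collected data allow

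*Protocol article*

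**What the plan says.** Under Statistical analysis, Secondary outcomes, the article says that quality of life, fitness, biological and body composition outcomes "will use mixed effects models for data at all time points incorporating within-person correlation". It adds: "Within-person correlation of residuals will be handled by an autoregressive (AR1) error structure". For adjustment it says that "factors will also be added for the 2 stratification variables (centre, ADT duration" (the parenthesis closes there). It says nothing about the baseline value of the outcome.

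Under Post-intervention period outcomes, similar models are applied to FACT-F and 6MWT at three points: end of intervention, and three and six months later. Baseline is not among these points, and no baseline term is named. The same type of model is then extended to all outcomes over 12 months, to judge whether changes over time are similar and "whether differences between groups at any given time are clinically important".

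The co-primary section differs. Its model will "regress the change in FACT-F and 6MWT values between baseline and 6 months against the baseline value", together with treatment group and the strata, and the Fig. 3 legend repeats: "We will compare groups by means of ANCOVA using the baseline score as the covariate". The Randomization section places allocation after the baseline assessment.

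**The concern.** Because allocation follows the baseline assessment, any difference between arms at baseline is chance. A model can use that knowledge by conditioning on baseline or by giving both arms one baseline mean. A standard arm-by-visit model does neither unless told to. With a free baseline mean in each arm, the arm difference in change is a plain change-score contrast, and the arm difference at a visit is a raw follow-up contrast that carries the chance imbalance.

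Three things are at stake:

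- The article expects 200 participants to give accurate estimates for secondary outcomes and judges clinical importance from 95% confidence intervals. Intervals wider than the data require work against both.
- FACT-F and 6MWT at 6, 9 and 12 months would each have two estimates: the baseline-adjusted comparison repeated at each follow-up under Co-primary outcomes, and the mixed-model estimate with no baseline term named. The two can differ.
- BMD is measured only at baseline and 12 months. With complete data and free arm means, its model reduces exactly to a change-score or a raw follow-up contrast.

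**Working it through.** **The plan's own figure.** The only stated figure is 81% power with 100 per arm for the two co-primary outcomes. It cannot be reproduced, because the margin and SD are in Additional file 4. At one-sided 0.025 it implies margin/SD = (1.960 + 0.878) × √(2/100) = 0.40. It concerns analyses that already adjust for baseline, so this point does not affect it. No precision figure is given for secondary outcomes.

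**Inputs.** From the article: 1:1 allocation, 100 per arm, visits at 0, 3, 6, 9 and 12 months, AR1 errors. Assumed: complete data, equal variance at each visit, and a correlation *r* between baseline and follow-up, for which the article gives no value.

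**Formulas.** Variance of the arm contrast in units of 2·SD²/n:

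- same-visit difference: 1
- change from baseline, free baseline means: 2(1 − r)
- baseline-adjusted: 1 − r²

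Adjustment therefore cuts variance by 1 − (1 − r²)/[2(1 − r)] = (1 − r)/2 against the change contrast, and by r² against the same-visit difference.

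| r (assumed) | Change | Adjusted | Cut against change | Cut against same-visit |
|---|---|---|---|---|
| 0.3 | 1.40 | 0.91 | 35% | 9% |
| 0.5 | 1.00 | 0.75 | 25% | 25% |
| 0.7 | 0.60 | 0.51 | 15% | 49% |
| 0.8 | 0.40 | 0.36 | 10% | 64% |

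**Under the article's error structure.** Take AR1 with an assumed correlation of 0.8 over three months, so r = 0.8² = 0.64 at 6 months and 0.8⁴ = 0.41 at 12 months. Standard errors in SD units with 100 per arm:

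- Same-visit, any time: √0.02 = 0.141.
- 6 months: change √(0.02 × 2 × 0.36) = 0.120; adjusted √(0.02 × (1 − 0.64²)) = 0.109.
- 12 months: change √(0.02 × 2 × 0.5904) = 0.154; adjusted √(0.02 × (1 − 0.4096²)) = 0.129.

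At 12 months the change contrast is less precise than ignoring baseline, and its variance is 1.42 times the adjusted one (2/(1 + 0.4096)).

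**Baseline as a response.** Generalised least squares on all five visits, with baseline as a response and one baseline mean for both arms, also gives 0.109 at 6 months and 0.129 at 12 months, identical to ANCOVA. The loss comes only from free baseline means or from unadjusted same-visit contrasts.

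**The case against.** The strongest objection is that the article does not state the mean structure of these models. It gives no arm-by-visit term and does not say whether baseline means are free or common. If they were constrained equal, nothing would be lost. The parameterisation might also be set out in a fuller document that is not shown. The first part stands: free baseline means are an inference from the text. But the article does not simply defer the model. It fixes the data, the error structure and the stratification factors, and it leaves out the one adjustment that it writes explicitly for the co-primaries. An equal-mean constraint has to be specified deliberately, and the three-visit post-intervention model does not list baseline at all.

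A reader might infer more than the article supports:

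- **That using baseline as a response is the error.** It is not; the constrained model does the same and matches ANCOVA.
- **That the strata are the only covariates.** They are the only adjustments named. The wording is not exhaustive, and Table 1 labels haemoglobin and HbA1c as covariates without assigning them to a model.
- **That the results would be biased.** Under randomisation both the change contrast and the same-visit contrast are unbiased.
- **That the loss is always large.** The two losses move in opposite directions with *r*. The largest figures belong to whichever contrast is less efficient at that correlation, and at r = 0.8 the saving against change is 10%.

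It is also fair to say that these analyses carry no decision rule or stated power, and that the co-primaries already have a baseline-adjusted comparison at each follow-up.

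**Conclusion.** The point holds as one of efficiency and consistency. The sections on secondary and post-intervention outcomes name centre and ADT duration and no baseline adjustment, unlike the co-primary ANCOVA. Followed as written, they give arm contrasts that are unbiased but less precise than the collected data allow. The unadjusted variance is 1.11 to 1.54 times the adjusted variance for a change contrast (r = 0.8 down to 0.3) and 1.10 to 2.78 times for a same-visit difference (r = 0.3 up to 0.8). This rests on complete data, equal variances, assumed correlations, and the plain reading that arm means are free at each visit or that baseline is absent. If baseline means are in fact constrained equal, the ratio is 1.00 for the models that include baseline. No stated figure is wrong, and the co-primary conclusion is not affected.

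**What to change.** State in both sections how each outcome's own baseline enters the model, by one of two routes:

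1. as a covariate, with post-baseline visits only as responses; or
2. as a response, with the baseline mean constrained equal across arms (constrained longitudinal data analysis), which is justified because randomisation follows the baseline assessment.

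In either case include arm-by-visit terms and both stratification factors, and report arm differences from that model. For the post-intervention models of FACT-F and 6MWT, the value to use is the pre-randomisation baseline. The 6-month value is post-randomisation, so the equal-mean constraint does not apply to it.

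The change is to analysis wording only. It needs no new data, does not alter who is analysed, and brings these models into line with the co-primary ANCOVA.
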